
### Data management

2.11

The ENERGYCO project will utilize three main systems to store and manage data. First, the Dropbox platform will be used to manage all project-related information, including monitoring documents, evaluation protocols, participant tracking sheets, adverse event control sheets, and raw data for all analyzed variables (both primary and secondary), organized into separate spreadsheets based on the variable being studied. Second, all data will be stored on an external hard drive, kept securely in the principal investigator’s office. The same data and folders stored in Dropbox will also be mirrored on this physical hard drive. Third, informed consent forms, paper-based questionnaires, and participant evaluation sheets will be collected and stored in paper format in the principal investigator’s office. To ensure participant anonymity, each individual will be assigned a unique code upon submitting their informed consent, which will be used in all data reports. The principal investigator will have continuous access to the final dataset and the research staff undertakes not to store on its computer any data related to the ENERGYCO project. Regarding data quality control, the process will include double-checking paper-based evaluation sheets and reviewing the ranges and valid values in the resulting spreadsheets. The research team will perform quality controls and archive the data following a pre-established protocol for both the baseline and follow-up phases. If any data quality issues are detected, the raw data stored in Dropbox or the hard drive will be consulted, along with the paper-based records, which will be reviewed as needed. It is important to highlight that the ENERGYCO project is committed to publishing its findings, whether positive, negative, or inconclusive, in peer-reviewed journals, at national and international conferences, and through public dissemination in local, regional, and national media outlets, as well as on social media platforms. Additionally, these results will be shared with participants and schools through individual reports for participants and comprehensive reports for the schools, including corresponding interpretations of the findings. Finally, eligibility for authorship will be determined by the principal investigator in accordance with the guidelines of the International Committee of Medical Journal Editors (ICMJE), which require substantial contributions to the conception, design, data acquisition, analysis, or interpretation, as well as drafting or critically revising the manuscript and approving the final version.

## Discussion

3

To the best of our knowledge, the ENERGYCO study will be the first study which will assess the PAEE related to different modes of commuting to school using indirect calorimetry. Moreover, the effects of an eight-week school-based cycling intervention on RMR and PAEE, as well as on other physiological (i.e., basal heart rate, blood pressure, and body temperature), physical (i.e., PA levels, anthropometric measures, body composition, physical fitness, and motor competence), and psychosocial outcomes(e.g., perceived barriers to active commute to school, self-esteem, and mental health) among Spanish adolescents aged will be assessed. The main objective of the study has potential individual implications for adolescents, as the school-based cycling intervention aims to explore its effects on RMR and daily PAEE, which may contribute to changes in PA levels and associated physical, psychosocial, and emotional aspects. However, individual variability and adherence challenges must be considered when interpreting the results. To support engagement, the study will provide easy-to-use encouragement strategies, such as infographics and motivational videos, to promote adherence to the intervention (i.e., cycling at least 3 days to and from school). While these materials may help sustain participation, their effectiveness in maintaining long-term engagement remains to be explored.

The findings of the ENERGYCO study will contribute to the current understanding of the potential effects of a school-based cycling intervention on RMR and daily PAEE among adolescents. Unlike most studies assessing ACS, PAEE, or PA levels, which often rely on self-reported tools, this study will use objective measurement techniques. Nevertheless, current research is incorporating objective devices such as GPS and accelerometry for more precise measurements (94). In this study, in addition to using these devices, indirect calorimetry technique will be employed, adding further value to the research. Furthermore, we will analyze the effects of a school-based cycling intervention on increasing RMR in adolescents, instead of focusing on a behavioral change. Indeed, most interventions in the school context have been focused on changing the behavior of adolescents (36–39), but even though such interventions are necessary, we still do not know in depth the effects on some health variables, especially on physiological outcomes such as RMR and PAEE. Therefore, the ENERGYCO study is expected to provide novel insights into the potential effects of a school-based cycling intervention on RMR and PAEE, along with other physiological, physical, and psychosocial outcomes. As research in this area remains limited, this study will contribute valuable data. Nevertheless, the findings should be interpreted in the context of the study’s duration, sample characteristics, and variability in adherence among participants. In this sense, and following the previous literature, interventions with a duration of 8 weeks could be enough to improve health markers in young people (95, 96).

Furthermore, studies focus on assessing the PAEE related to ACS in free living conditions have used accelerometer counts (20, 97) or heart rate (12) instead of indirect calorimetry. Indeed, as far as we know, two studies focus on young population used indirect calorimetry to measure the PAEE associated to different routine activities (98) or just walking in a treadmill (99), but both of them were carried out under laboratory conditions. The study by Schuna et al. (98) involved 106 American children and adolescents (6 to 18 years old) who completed a series of activities such as sitting, watching movies, coloring, climbing stairs, playing basketball, or jumping. Authors concluded that the lowest average PAEE values were associated with sitting and watching movies, while jumping was the activity that caused the highest average PAEE. While the study by Tudor-Locke et al. (99) evaluated the cadence produced by different walking speeds (an indirect measure of intensity) in young people aged 6 to 20 in a controlled trial. Participants completed multiple 5-min series on a treadmill, ranging from 0.80 km/h to 8.04 km/h. Steps were counted visually, and intensity was objectively measured using a portable metabolic system. Therefore, the ENERGYCO study will contribute to advancing knowledge on PAEE associated with different modes of commuting to school. To our knowledge, this will be the first study to objectively measure PAEE in adolescent commuters using indirect calorimetry in free-living conditions.

The ENERGYCO study aims to provide valuable insights for policymakers, educators, urban planners, and public health professionals by offering concrete recommendations for adapting and implementing similar interventions in different educational and urban settings. In the school context, integrating ACS into curricula through road safety education and awareness campaigns on the health benefits of cycling could enhance engagement. Policymakers should support these efforts by incorporating ACS modules into Physical Education programs and fostering collaborations between schools and local authorities to ensure safe commuting environments. From an urban planning perspective, expanding cycling infrastructure around schools, such as protected bike lanes, traffic-calming measures, and secure bicycle parking, should be prioritized, along with establishing urban design guidelines to improve the accessibility and safety of school routes. Public health initiatives should encourage community-based interventions, including bike-to-school programs, incentive schemes for cycling equipment, and partnerships with local businesses to create cycling-friendly environments. Regarding scalability and sustainability, after the completion of the ENERGYCO study, a comprehensive review of the collected data will be conducted to explore how a more cost-effective assessment approach could be developed. Given the logistical challenges of school settings, this analysis will focus on identifying ways to streamline data collection while maintaining methodological rigor, ensuring feasibility for future studies. The goal will be to refine the assessment of RMR, PAEE, and secondary outcomes in a real-world school environment. To maximize impact, the ENERGYCO study will disseminate its findings through infographics and policy briefs tailored to families, schools, municipalities, and public health entities, ensuring accessibility and usability for decision-makers.

It is important to mention that the ENERGYCO protocol presents some limitations and risks that may arise in the future. These limitations will be: (i) some participants may not attend the assessments, which could lead to a small sample size; (ii) the relatively small sample size in Phase I, which could potentially limit statistical power and generalizability. The sample size was determined based on previous studies using indirect calorimetry in similar research contexts. However, the complexity of the data collection process posed significant challenges for recruitment; (iii) important outcomes such as distance or barriers to cycling to school may also influence the recruitment process, resulting in a low-rate recruitment; (iv) there may be problems with the selection of schools. In Phase II, after the selection of schools, it is possible that there may not be enough students to form each of the groups to low prevalence of cycling to and from school in Spain (46); (v) the family is not involved in the intervention, uncertainties surrounding the help that the school can give to the research group for the success of the intervention (e.g., contact with adolescents). On the other hand, the ENERGYCO protocol presents several strengths. The study design is a cluster randomized controlled trial, as well as the duration of 8 weeks of the school-based cycling intervention, including strategies for maintaining adherence and motivation, and an incentive system. The use of instruments gold standard, such as the Omnical for assessing the RER, or the use of indirect calorimetry for measuring the PAEE related to different modes of commuting will provide accurate data for these variables.

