**Conclusion:**

The ENERGYCO study will provide novel insights into the PAEE associated with different modes of commuting to school using indirect calorimetry, as well as a comprehensive overview of how an 8-week school-based cycling intervention impacts resting energy expenditure, daily energy expenditure, and the physical and psychosocial health of adolescents.

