
Furthermore, ACS interventions have primarily been conducted in children (i.e., from 6 to 11 years) rather than in adolescents (i.e., from 12 to 17 years) as well as promoting walking rather than cycling. These interventions have primarily focused on changes in the mode of commuting, frequency of commuting, or increased PA levels (36–39) rather than assessing the effects on 24-h energy expenditure components (i.e., RMR and PAEE). In addition, interventions to improve RMR or PAEE have mainly consisted of resistance or endurance trainings (5, 11), being these activities performed out of school. To the best of our knowledge the effect of a school-based cycling intervention on the RMR and daily PAEE of adolescents has not been studied to date. In fact, the assessment of the effects of a school-based cycling intervention could be particularly important to consider as a suitable strategy to increase the RMR and re-balance PAEE in the adolescent population. In addition, a school-based cycling intervention will not only produce effects at physiological level (i.e., RMR or PAEE), but it will also allow to deepen the effects of this mode of commuting to school at physical or psychosocial level in the adolescent population. It has been shown that cycling to school is associated with greater grip strength and vertical jump (40), but the association does not imply causality. Similar results occur at the psychosocial level, where cycling to school has been associated with greater well-being or increased social relations compared to use passive passively commuting to school in adolescents (41). Moreover, there is controversy as to whether cycling to school could improve young people’s body composition (14). Thus, a school-based cycling intervention is needed to increase and improve the evidence of the effects of cycling to school in physiological, physical, and psychosocial outcomes.

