Therefore, this protocol describes the rationale and methodology of the ENERGY expenditure of school Commuting study (The ENERGYCO study). ENERGYCO project will address the gaps and limitations in the existing scientific literature regarding the PAEE that occurs during cycling to school. Considering the previous literature and existing gaps, the ENERGYCO project will be divided into two phases. Phase I will focus on using a portable metabolic system to assess PAEE associated with different modes of commuting (i.e., walking, cycling, motorized vehicles) under free-living conditions in Spanish adolescents. Additionally, Phase I will serve to develop a predictive equation that will be used in Phase II to measure PAEE associated with different modes of commuting to and from school. Additionally, considering the ongoing debate regarding the health benefits of ACS and the scarcity of studies examining the effects of school-based cycling interventions on RMR and PAEE, the Phase II will aim to assess the effects of a school-based cycling intervention on RMR and PAEE, as well as on other physiological (i.e., basal heart rate, blood pressure, and body temperature), physical (i.e., PA levels, anthropometric measures, body composition, physical fitness, and motor competence), and psychosocial outcomes (e.g., perceived barriers to active commute to school, self-esteem, and mental health) on Spanish adolescents. It is hypothesized that, in Phase I, using a portable metabolic system under free-living conditions will provide accurate and distinct measurements of PAEE associated with different commuting modes in Spanish adolescents. Specifically, we hypothesize that these measurements will highlight significant differences in PAEE across commuting modes, offering a more precise understanding of how commuting impacts adolescents’ physical activity levels. Additionally, we expect the data collected in Phase I to contribute to the development of a valid and reliable predictive equation for estimating PAEE during commuting to and from school. we hypothesize that a school-based cycling intervention will lead to a significant increase in both RMR and PAEE compared to a control group. We further hypothesize that the intervention will improve physiological outcomes (e.g., reductions in basal heart rate), physical outcomes (e.g., enhanced physical fitness and motor competence), and psychosocial outcomes (e.g., increased self-esteem) among Spanish adolescents.

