### Study population

2.2

In the Phase I of the ENERGYCO study, a convenience sample of 50 students (12–16 years old) will be recruited to assess the PAEE of different modes of commuting to school (i.e., walking, cycling, and motorized-vehicle). For Phase II, the ENERGYCO study will recruit a random sample of students (*n* = 300) from the three Spanish cities (i.e., Granada, Almería, and Jaén). The intervention aims to assess the effects of a school-based cycling intervention in the RMR and PAEE related to cycling to school, as well as its impact on others physiological, physical, emotional, and psychosocial outcomes in Spanish adolescents. The randomization process is presented in Figure 1.

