
**Figure 2 fig2:**
[figure not shown]
Complete phase I protocol showing the three controlled environment simulations (i.e., commute by motorized-vehicle [from phase 2 to phase 2.2], walking [from phase 3 to phase 3.2], and cycling [from phase 4 to phase 4.1]).

In the Phase II, the procedures of the intervention will be tested as a pilot phase to ensure its feasibility and effectiveness. Prior to this, the research team will undergo joint training for internal evaluation. The pilot phase will be implemented in adolescents from a school in Granada over 2 days, with the involvement of the entire research team, lasting approximately 1 h per day. In this pilot phase, the organization of evaluations and the effectiveness of the tests used will be observed by the research group. Moreover, the school-based cycling intervention, which will be described in detail later, will be designed by research personnel trained as Physical Education teachers and graduated in Sport Sciences, and subsequently reviewed by research experts. During the baseline and follow-up of Phase II, the RMR, along with various health-related outcomes, will be assessed. These include individual, social, environmental, and safety factors associated with ACS (see Table 3). Figure 3 outlines the assessments to be conducted during the baseline and follow-up periods.

**Table 3 tab3:** Summary of the variables and instruments phase I and PHASE II.

Section	Variables	Instrument	Phase I	Phase II
Primary outcomes				
Physiological outcomes	Resting metabolic rate	Omnical (Maastricht Instruments, Maastricht, The Netherlands)		X
	Energy expenditure	Cosmed K5 (Cosmed, Rome, Italy)	X	X
Secondary outcomes				
Socio-demographic characteristics	*Students:* Age, school grade and class, gender, full postal address, bicycle owners	Student questionnaire	X	X
	*Parents:* School, name, age, gender, children’s gender, and full postal address, parental education level	Family questionnaire		X
Physiological outcomes	Blood Pressure	Stethoscope		X
	Heart rate	Polar Ignite 10, chest band and watch (Polar Electro Oy, Kempele, Finland)	X	X
	Body temperature	Ibuttons (Maxim/Dallas Semiconductor Corp., USA)	X	X
Physical outcomes	*Physical activity levels*	Accelerometer ActigraphGT3x+	X	X
		Youth Activity Profile questionnaire (YAP)		X
	*Physical fitness* Cardiorespiratory capacity			X
	Muscular strength	Course Navette		X
	Physical literacy	Analog dynamometer		X

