##### Energy expenditure related to active commuting to school

2.7.1.2

PAEE related to different modes of commuting to school (i.e., walking, cycling, passive modes) will be measured using the Cosmed K5 portable metabolic system in Phase I. The Cosmed K5 has previously shown a good level of agreement compared to stationary metabolic carts at low cycling intensity (5.8% difference in VO_2_). At moderate intensities, it slightly underestimated VO_2_, VCO_2_, and energy expenditure (~6.6–6.9%). Additionally, during walking tests, the Cosmed K5 demonstrated high reproducibility, with a coefficient of variation of 4.5% for energy expenditure per kilometer and a concordance coefficient of 0.91. VO_2_ measurements were consistent, with low variability in the fraction of expired oxygen (coefficient of variation of 0.9%) (56). The Cosmed K5 is worn on the back with a harness and measures oxygen consumption (VO_2_) and carbon dioxide production (VCO_2_) in breath-by-breath mode. Before each assessment, the device will be calibrated using a reference gas mixture of 15.92% O_2_ and 5.03% CO_2_. Delay calibration for the breath-by-breath mode will also be performed (57). During the test, participants will breathe normally while commuting, and the Cosmed K5 will record data continuously. Data will be analyzed as the mean VO_2_ and VCO_2_ (ml/min) during each commuting mode. In Phase II, PAEE related to cycling will be estimated using predictive equations developed in Phase I. These equations will incorporate variables such as distance, speed, and heart rate, and will be cross-validated against PAEE measurements obtained with the Cosmed K5 to ensure accuracy. Therefore, data will be analyzed as the mean VO_2_ and VCO_2_ (ml/min) during each cycling trip to and from school, aggregated by participant during the intervention period.

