##### Trip characteristics

2.7.2.18

ACS behavior will be objectively evaluated over seven consecutive days using a Q-STARZ BT-Q1000XT GPS device, manufactured by Int Co., Ltd. (Taipei, Taiwan). The GPS will record distance, speed, and trip duration for each commute performed by the participants. Additionally, environmental variables such as terrain slope will be measured and later used as confounders in the analysis. The GPS will be configured with a 15-s epoch to ensure precise data collection. This protocol, which combines GPS data with accelerometry for analyzing ACS behavior, has been previously validated by our research group (17, 20, 31). In this project, the combination will also be used to estimate PAEE associated with different modes of commuting to school. The main variables of interest include distance (km), average speed (km/h), and trip duration (minutes). Data will be aggregated by participant and collected during baseline and follow-up assessments.

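### The Phase II primary PAEE has inconsistent targets, and its only working definition cannot support the planned comparison with control

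*Protocol article*

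**What the plan says.** The Introduction hypothesises that RMR and PAEE will both increase compared with control, and Table 3 lists RMR and energy expenditure as the primary outcomes. What PAEE covers in Phase II changes from place to place.

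- **Whole day.** The Discussion says that "the school-based cycling intervention aims to explore its effects on RMR and daily PAEE", and its next paragraph repeats the daily wording. The Abstract's conclusion promises to show how the intervention "impacts resting energy expenditure, daily energy expenditure, and the physical and psychosocial health of adolescents". The Introduction states the gap in the same terms: "the effect of a school-based cycling intervention on the RMR and daily PAEE of adolescents has not been studied to date".
- **Cycling to school.** Section 2.2 gives the aim as "effects of a school-based cycling intervention in the RMR and PAEE related to cycling to school". Section 2.7.1.2 agrees: "In Phase II, PAEE related to cycling will be estimated using predictive equations developed in Phase I". It then defines the variable as average VO2 and VCO2 (ml/min) over cycled trips, combined per participant across the intervention period.
- **All commuting modes.** The Introduction says the Phase I equation will be "used in Phase II to measure PAEE associated with different modes of commuting to and from school". Section 2.7.2.18, on GPS with accelerometry at baseline and follow-up, says that "the combination will also be used to estimate PAEE associated with different modes of commuting to school".

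Table 3 marks the Cosmed K5 for Phase II, although section 2.7.1.2 uses equations there. It appears to mark GPS trip characteristics for Phase I only, although sections 2.6.1 and 2.7.2.18 collect them in Phase II.

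Section 2.10.2 specifies ANCOVA of the post-intervention value on group, with the baseline value as covariate. It names PAEE as a main outcome without saying which PAEE.

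**The concern.** A primary outcome needs one stated quantity, defined for every randomized participant at the times the model uses. Here the headline quantity (daily) has no stated measurement, and the quantity with a definition (cycled trips) exists mainly in the intervention arm.

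Two things are at stake. A conclusion about daily energy expenditure would rest on no prespecified variable. And a positive PAEE for cycled trips would largely restate that the intervention arm cycled. It would not show that the participants expended more energy, because the ride may replace a walk. Table 2 excludes only those who cycled to school more than three days a week in the past year, so habitual walkers can enter.

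**Working it through.** The plan gives no PAEE figure to reproduce. The check sets targets against measurements and then uses the protocol's own speeds.

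**1. Does each target have a measurement?**
- Daily PAEE: none stated. The equations cover trips, and section 2.7.2.5 reduces the seven-day accelerometer record to average daily MVPA time.
- Cycling PAEE: Phase I equations using distance, speed and heart rate (section 2.7.1.2).
- All-mode commuting PAEE: the equations or GPS with accelerometry, but no unit or summary is given.

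**2. Can the section 2.7.1.2 variable enter the ANCOVA of section 2.10.2?**
- Follow-up value in controls: they keep their usual habits (section 2.5), and section 2.4.2 notes that cycling to school is uncommon in Spain. Most would have no cycled trip, so the mean rate is undefined, or zero by convention.
- Baseline covariate: the variable is defined over the intervention period, so it has no baseline value as written. Extended to the baseline week, it would be empty for most participants for the same reason.
- Inputs: section 2.7.2.2 records trip heart rate on cycled trips during the eight weeks. Section 2.7.2.18 records distance and speed over seven days at baseline and follow-up. The stated windows do not coincide.
- Section 2.10.1 requires valid baseline and follow-up PAEE in both arms for the per-protocol set. Read literally with this variable, most controls could not qualify.

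**3. Is it an amount of energy?** A mean in ml/min is a rate. Take two participants with identical trips and the same mean rate. One cycles 3 days a week: 3 × 2 × 8 = 48 trips. The other cycles 5 days a week: 5 × 2 × 8 = 80 trips. The second expends 80/48 = 1.67 times as much, yet both have the same outcome value.

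**4. Does more cycling PAEE imply more commuting PAEE?** Inputs from section 2.6.1: walking 4.4–4.6 km/h, cycling about 15 km/h, distance 1,350 m.
- Walking time: 1.35/4.6 × 60 = 17.6 min to 1.35/4.4 × 60 = 18.4 min.
- Cycling time: 1.35/15 × 60 = 5.4 min.
- Time ratio: 15/4.6 = 3.26 to 15/4.4 = 3.41, whatever the distance.

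Let r be the net energy rate of cycling divided by that of walking. For a walker who switches, trip energy changes by the factor r/3.41 to r/3.26. The document does not give r, so a range is assumed:

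| r (assumed) | cycled / walked trip energy | change |
|---|---|---|
| 1.5 | 0.44–0.46 | −56% to −54% |
| 2 | 0.59–0.61 | −41% to −39% |
| 3 | 0.88–0.92 | −12% to −8% |
| 4 | 1.17–1.23 | +17% to +23% |

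**5. At group level.** Assume passive commuting has net cost zero, distances are equal, and everyone switches to cycling. With a share s of baseline walkers, the mean change is proportional to r/(time ratio) − s. It is zero when s equals the factor in the table: about 45% walkers at r = 1.5, 60% at r = 2 and 90% at r = 3. The document gives neither r nor s.

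**The case against.** The strongest defence is that section 2.7.1.2 governs. It stands under the primary outcomes, it is the only place with a method, unit and summary, and the aim in section 2.2 agrees with it. The daily wording is in the Abstract's conclusion, the Discussion and a sentence about the literature gap. This stands as a reading of rank, but it does not rescue the plan: steps 2 and 3 show that the governing definition is the one that cannot be analysed as planned.

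Four stronger readings are tempting, and the document does not support them.

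- **Cycling PAEE and commuting PAEE will move in opposite directions.** This is possible but not shown. It depends on r and on the walker share, and the percentages in step 4 describe one walker who switches, not the arm contrast.
- **No contrast decides the trial because of PAEE.** RMR is also primary and no order is stated between the two. Settling PAEE would leave that open, so it cannot be blamed on PAEE alone.
- **There are three rival methods.** The K5 entry may be only a table mark to correct, and the GPS data of section 2.7.2.18 may simply supply the equation with distance and speed. The Introduction's reservation about accelerometers concerns count-based estimates.
- **There are no whole-day data.** Whole-day accelerometry is collected at both times. What is missing is a stated route from it to daily PAEE.

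**Conclusion.** The concern holds. The Phase II primary PAEE is described as daily, cycling-only and all-mode. The daily version has no stated measurement. The cycling version is a rate without a meaningful value for most controls or at most baselines, so it can support neither the baseline-adjusted ANCOVA nor the hypothesis against control. This is a contradiction within the text on a primary outcome, not a detail left for an analysis plan.

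The firm number is the 3.3–3.4 multiple, which rests only on the protocol's speeds. The percentage changes and walker shares are illustrations under assumed r, zero passive cost and equal distances. That most participants do not cycle at baseline, and most controls not at follow-up, is inferred from eligibility, the control condition and the stated low prevalence; no share is given. Figure 3, which outlines the assessments, was not available for this check.

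**What to change.** Name one Phase II PAEE variable that is measurable in both arms at baseline and follow-up. One workable choice is total commuting PAEE per school day (kcal/day, all modes), predicted by mode-specific Phase I equations from distance and speed in the GPS weeks. Then:

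- Use heart rate in the equation only if the monitor is also worn on all trips in those weeks. At present trip heart rate is planned for cycled trips only.
- State where the follow-up GPS week falls relative to the eight weeks. If it comes after them, it may miss the cycling that section 2.7.1.2 targets.
- Make the cycling-trip variable secondary and descriptive within the intervention arm.
- Reconcile Table 3 (the K5 mark for Phase II and the GPS trip mark for Phase I only) with sections 2.6.1, 2.7.1.2 and 2.7.2.18.
- Replace the daily wording with commuting PAEE in the Abstract's conclusion and the Discussion, align the Introduction and section 2.2, and name the variable in section 2.10.2.

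The cost is mainly wording and a derivation from the planned GPS weeks, plus extra monitor wear if heart rate is kept. The claim narrows from daily to commuting energy expenditure, and the equation may lose heart rate as a predictor. The ranking of PAEE against RMR is a separate decision.
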